**Implementation phase**					
Evolution of the processes and integration	FG	II			DR
Identification of problems and failures (C)	FG	II			
Fidelity of the intervention (I)					IFC
**Post-implementation phase**					
Opinion about the implementation process (C)	FG-II	II	FG	FG	
Identification of obstacles and facilitating elements (C)	FG-II	II	FG	FG	
Description of the impact on stakeholders/organizations (E)	FG-II	II	FG	FG	
Satisfaction with the intervention (E)	DG-II	II	DG	DG	

C: Context; I: Intervention; E: Effects.

FG: Focus group; II: Individual interview; DR: Documentation review; IFC: Intervention fidelity checklist.

#### Data collection strategies

A multiple-case study [49] will be performed with multiple sources of information. Such a strategy is particularly appropriate for analyzing the context and the mechanisms involved [50,51]. Each FMG will be considered a case with its own context, and will include its interactions with partners. This study will be conducted with a multifaceted approach before, during and after the intervention. As described in Table 1, four categories of key informants will be interviewed: (1) FMG stakeholders (doctors/nurses); (2) managers (FMG/CSSS); (3) participating patients and their families; (4) identified partners of case management (CSSS professionals, representatives of community organizations and community pharmacists), as well as volunteer leaders of self-management groups. Four strategies for collecting data will be used: (1) focus groups; (2) individual interviews; (3) review of documents produced during the implementation of the intervention, (4) an intervention fidelity checklist. Interview guides with open-ended questions that are adapted to each category of key informants will be developed and validated by implementation evaluation experts.

The pre-implementation phase will describe the context of the intervention regarding: (1) the characteristics of the environment (contextual factors); (2) the operation and integration of existing services, as well as participant satisfaction; (3) the issues related to the implementation as identified through group discussions. Focus groups will involve FMG doctors (n = 6, one group per FMG), patients and their families (n = 4 patients, one group per FMG; n = 4 family members, one group per FMG) and partners considered to be key participants (n = 4). Individual interviews will be conducted with FMG and CSSS managers (n = 6) and FMG nurses (n = 8).

The implementation phase will identify the changes in FMG processes (mechanisms) and the integration of services mid-way through the implementation in addition to learning about the obstacles and challenges encountered, as reported through focus groups with FMG stakeholders (n = 6) and obtained from individual interviews with FMG and CSSS managers (n = 6). Documentation from meetings of the advisory committee and from meetings between the Clinical Project Coordinator and nurses or managers, etc., will be obtained and analyzed in order to identify obstacles and challenges, and adjustments made along the way. An evaluation of the fidelity of the intervention will be conducted to document the degree to which the intervention was implemented; this will vary with the needs of participating patients [52]. After each encounter, nurses will conduct the evaluation for participating patients using a standardized checklist that includes the case management criteria and follow-up parameters, the details of ISP, the number of interdisciplinary meetings, the partners called upon and their involvement, and the number of self-management support meetings. These reports will help determine whether the interventions have conformed to the original study model.

The post-implementation phase will describe the implementation process, the obstacles and enabling factors, the effects of the intervention on stakeholders/organizations, and the satisfaction of key players. This will be accomplished through focus groups with FMG physicians (n = 6), patients and their families (n = 8) and partners considered key informants (n = 4), and individual interviews with FMG and CSSS managers (n = 6) and with FMG nurses (n = 8).

#### Data analysis plan

Data collected from the key stakeholders will be analyzed in three steps according to a qualitative content analysis procedure to identify emerging themes and trends: coding, sorting of documentation by content, and analysis. Driven by the data, inferences will be drawn and information units will be compared [53]. This content analysis will be performed using NVivo software (Version 9) for data from individual and group interviews. In addition to seeking to reveal the themes that are specific to each element of the implementation evaluation (context, intervention, mechanisms of action, impact), the analysis at this stage aims to: (1) explain how different contexts have influenced the implementation of the intervention and the observed effects; and (2) identify elements to be considered in order to improve the intervention and promote its implementation in the other FMG [50]. The scientific rigour of this approach will be assured by recognized qualitative research strategies [54]. Credibility (accuracy of the description of the phenomenon) will be assured by open-ended questions, allowing participants some latitude in what they want to reveal and by the triangulation of informants. Reliability (accuracy with which we account for various perceptions expressed by participants) will be assured by data coding by at least two members of the research team with expertise in different domains (triangulation of researchers). Validation (confirmation of the analysis and interpretation) will be assured through extensive documentation of the analysis process. Transferability (transfer of the outcomes to other settings or populations) will be assured by the detailed description of the context and participants.

### Evaluation of the effects

The evaluation of the effects on patients will be based on a pragmatic randomized experimental design with delayed intervention for the control group and measurements taken before and after the intervention (at six-month follow-up). This allows to evaluate interventions in actual clinical settings to maximize their generalizability [55]. Implementation analysis will document how different contexts influenced the implementation and the observed effects. The before/after experimental design is a robust method for observing the potential effects of the intervention [56]. The design also includes an assessment regarding use of services over a year in the experimental group.

#### Study population

Targeted patients will be those described in the objectives. The concept of vulnerability will be operationalized by considering both the frequency of the CSSS care use (emergency room visits and hospitalization) and patient vulnerability characteristics, based on the judgment of the primary care team in the FMG. This combined approach was proposed as a more favourable strategy for patient identification for this kind of intervention, when compared to using each one of these strategies in isolation [57]. Steps to target the most vulnerable participants will include: 1) Presentation of the intervention to FMG primary care physicians and nurses, 2) Delivery of a computerized list (obtained using MAGIC Chronique software by MédiaMed Technologies [58]) of the 300 most frequent users of CSSS services (emergency department visits and hospitalizations) having at least one of the targeted CD in each FMG. FMG professionals will then identify the 100 patients they believe will benefit most from the intervention described. The software used for patient identification will serve as a system to support decision-making for primary care teams who did not have access to this kind of information up till now.

After verifying patient eligibility and obtaining their consent, participants will be allocated to one of two groups (experimental or control) according to a three-stage randomization process [59]: (1) generation of the patient allocation sequence using a simple randomization procedure; (2) allocation blinding (sequentially numbered and sealed in opaque envelopes); (3) assignment of participants by opening the envelopes at the time of recruitment. The experimental group will consist of a sample of 50 patients in each of the four FMG (n = 200). These patients will receive the intervention for six months. Patients in the control group (n = 200) will receive the usual care for six months and then the same intervention as the treatment group for the following six months (waiting list control group) [60]. This is intended to avoid the problem of demoralization of the control group, in addition to ensuring fair treatment among participants in both groups.

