#### Sample size and statistical power

When analyzing quantitative data, we must take into account that part of the effect is potentially associated with each of the eight case management nurses. The intra-nurse or intracluster correlation (ρ) is unknown, however, and is specific to each variable. On the other hand, given that series of standardization measures will be implemented to minimize nurse-specific effects, we anticipate that the intracluster correlation will not be higher than 0.10. Sample size was therefore calculated using this maximal anticipated ρ-value. Results indicated that a standardized effect size (ES) of 0.5 (qualified as medium [73]) will be detectable with two groups of 200 participants (25 per nurse) for a two-tailed test with the α level set at 0.05 and a power of 80% [74]. An ES of at least this magnitude can be expected since it was observed in a previous study [75] and in unpublished data from the CSSS de Chicoutimi. An ES of at least 0.5 also represents the clinically significant effect needed to justify the pragmatic integration of the intervention into the services already provided. For example, in the case of patient empowerment, the ability to detect an ES of 0.5 translates into the capacity to detect any difference of at least half a point within different domains of the heiQ, since the overall standard deviation is about 1 point [76]. The detection of smaller differences is irrelevant since it is not clinically significant.

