### Data analysis plan

All statistical analyses will be performed based on an intent-to-treat principle. We will first describe the characteristics of participants in each group, using means and standard deviations (continuous variables) or percentages (categorical variables). The groups will be compared at baseline (T0) using Student’s T test or the Chi-square test. Wherever possible, comparisons will be made between patients who agreed to participate in either phase of the study and those who refused, in order to document biases related to refusals. For outcome indicators at 3 months (self-efficacy, self-management practices, health habits, activation and psychological distress), groups will be compared at T1 using analysis of covariance adjusted for T0 scores. For indicators measured at six months (empowerment, quality of life and use of care), repeated measures analysis of variance will compare change over time in the two groups. In all cases, if the groups initially differ with regard to certain characteristics despite randomization, analysis will be adjusted to take into account the relevant variables. In addition, if a nurse effect is present (non-null intracluster correlation), despite efforts at standardization, multi-level analysis will be conducted to take this into account.

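### Simple randomization cannot be relied on to give the fixed 50 experimental patients per FMG, and naming exactly 100 patients per FMG leaves no stated margin for ineligibility or refusal

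*Protocol article*

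**What the plan says.** All but two of the statements stand in the protocol article under Study population, in this order.

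- The source list holds "the 300 most frequent users of CSSS services (emergency department visits and hospitalizations) having at least one of the targeted CD in each FMG".
- From it, "FMG professionals will then identify the 100 patients they believe will benefit most from the intervention described".
- Losses can occur only after that step: "After verifying patient eligibility and obtaining their consent, participants will be allocated to one of two groups (experimental or control".
- The method of allocation is "generation of the patient allocation sequence using a simple randomization procedure", with sealed, numbered, opaque envelopes. No blocking and no stratification by FMG is mentioned.
- The resulting arms are fixed: "The experimental group will consist of a sample of 50 patients in each of the four FMG (n = 200", and "Patients in the control group (n = 200) will receive the usual care for six months". Only the experimental number is written per FMG; 50 controls per FMG is an inference from the total of 200.

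Under Sample size and statistical power, an effect size of 0.5 "will be detectable with two groups of 200 participants (25 per nurse", at two-sided 5% and 80% power, with an intracluster correlation of at most 0.10. The 25 per nurse follows from 50 experimental patients and two nurses per FMG (Case management by FMG nurses).

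The Data analysis plan expects refusals: where possible, "comparisons will be made between patients who agreed to participate in either phase of the study and those who refused". No refusal rate is given.

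**The concern.** Two parts of one procedure do not deliver the sample that the same paragraph announces.

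First, a simple randomization sequence leaves the number of experimental patients per FMG to chance, while the text treats it as a fixed quota and carries it into the power calculation as 25 per nurse. Either the method or the quota is misdescribed. If staff were to hold the quota by departing from the sequence near the end, allocation would no longer be simple, and the last assignments in an FMG could be foreseen.

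Second, four FMG with 100 named patients each give 400, which is also the number to be randomized. Eligibility and consent come after naming, so as written there is no margin, and the text does not say whether a patient who declines is replaced from the other 200 on the list.

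At stake are the size of the trial and the planned numbers per FMG and per nurse.

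**Working it through.** **Inputs.** From the article: 4 FMG; 300 listed and 100 named in each; 200 per arm; effect size (ES) 0.5; intracluster correlation 0.10; 25 patients per nurse; 8 nurses; two-sided alpha 0.05. Uptake (eligible and consenting) is not given, so it is an assumption, varied from 60% to 80%.

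**1. The plan's own power figure.** Without clustering, n per arm = 2 × (1.960 + 0.842)² / 0.5² = 62.8, rounded up to 63. The design effect is D = 1 + (25 − 1) × 0.10 = 3.4. Power = Φ(ES / √(v₁ + v₀) − 1.960), where v = D/n for a clustered arm and 1/n for an unclustered one.

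- Both arms clustered: √(2 × 3.4 / 200) = 0.184; 0.5 / 0.184 − 1.960 = 0.75; power 77.4%. Exactly 80% would need 63 × 3.4 = 214 per arm.
- Experimental arm only: √((3.4 + 1) / 200) = 0.148; 0.5 / 0.148 − 1.960 = 1.41; power 92.1%.

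Neither gives exactly 80%. The baseline for any loss is therefore 77.4% or 92.1%.

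**2. Recruitment margin.** Named: 4 × 100 = 400. To be randomized: 200 + 200 = 400. Margin: zero. With uptake c and approach limited to those named, n per arm = 200c, patients per nurse = 25c and D = 1 + (25c − 1) × 0.10.

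| Uptake (assumed) | Randomized | D | Power, both arms clustered | Power, experimental arm only |
|---|---|---|---|---|
| 100% | 400 | 3.40 | 77.4% | 92.1% |
| 80% | 320 | 2.90 | 74.7% | 89.3% |
| 70% | 280 | 2.65 | 72.9% | 87.2% |
| 60% | 240 | 2.40 | 70.5% | 84.4% |

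The loss is about 3 to 7 points in the first case and 3 to 8 in the second. It is modest because losing patients also shrinks the cluster size.

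**3. Allocation.** At full uptake, the experimental number in an FMG is Binomial(100, 0.5), with standard deviation 5.

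- Exactly 50 in one FMG: C(100, 50) / 2¹⁰⁰ = 0.0796, or 8%.
- Exactly 50 in all four: 0.0796⁴ = 0.00004, or 0.004%.
- Exactly 200/200 overall: 4.0%.
- 95% range: about 40 to 60 per FMG (20 to 30 per nurse if the two nurses share equally), and 180 to 220 overall.
- At least one FMG outside 45 to 55: 72%.

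**4. Power cost of the imbalance.** In a simulation of simple randomization with 100 per FMG, both arms clustered and equal shares per nurse, mean power was 77.1%, against 77.4% with exact balance.

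**5. Names needed to randomize 100 per FMG.** 100/c = 125 at 80%, 143 at 70% and 167 at 60%. The list of 300 suffices down to about 33% uptake.

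**The case against.** The strongest reply is that the list leaves 200 reserves per FMG, that the text does not say identification stops at 100, and that the description of the case management component has family doctors helping to identify patients throughout. Replacement rules are the kind of recruitment detail that an article may leave to the full protocol. This stands in part: a reader might infer that the stated sample and power will be missed, but the documents do not show that. They show a procedure with no stated margin, and the shortfall is conditional on approaching only those named.

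A reader might also set the reduced power against the stated 80% and charge the whole gap to recruitment. That is not supported: with both arms clustered, power is 77.4% before anyone declines. Nor is clustering in both arms certain. The article ties the cluster effect to eight case management nurses, and 8 × 25 = 200 is the experimental arm alone. On that reading power stays above 80% at every uptake in the table.

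It is equally tempting to say that imbalance by FMG confounds site with treatment or overloads nurses. Imbalance under valid randomization is chance, not bias, and no caseload limit is stated. Nor is it a defect here that FMG is not named as a model term: the plan adjusts for baseline differences and allows multi-level analysis for nurses, and an analysis plan that is not shown may settle the rest.

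What remains is that the allocation method and the fixed quota do not match, and that the number named equals the number needed.

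**Conclusion.** The point holds in this limited form. Simple randomization and a fixed 50 experimental patients per FMG should be reconciled: even with 100 randomized in every FMG, the quota is met in all four with probability 0.004%, and 40 to 60 is the ordinary range. The main effect is on the planned numbers per FMG and per nurse and, to a small degree, on precision; validity is not affected.

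The recruitment step has zero margin as written. If decliners are not replaced, uptake of 80% to 60% leaves 320 to 240 randomized and costs about 3 to 8 points of power, depending on which arms are clustered. These figures rest on assumed uptake, an intracluster correlation of 0.10, equal numbers per nurse and the normal approximation.

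The allocation mismatch and the headcount follow from the text and are firm. The power loss is conditional.

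**What to change.** - **Allocation.** Replace simple randomization by permuted blocks stratified by FMG, with a separate envelope series per FMG and block sizes that vary, are not disclosed to recruiters and sum to 100. This gives 50/50 in each FMG once 100 are randomized. An equal split of the experimental patients between the two nurses then gives 25 each; blocking by FMG does not secure that by itself. Since FMG becomes a design stratum, include it in the outcome models.
- **Recruitment.** Have FMG professionals rank candidates from the list of 300, and invite in rank order until 100 are randomized in that FMG. At 80% to 60% uptake this means about 125 to 167 names. State that patients found ineligible or declining are replaced by the next in rank.

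The cost is a longer ranked list and four envelope series. The downside is small: some patients lower in the professionals' ranking are invited.

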### Measures

The variables defined within the logic model will be measured using instruments that are well known and have been validated in studies similar to the one proposed.

The proximal outcomes, evaluated at T0 (recruitment period), T1 (3 months) and T2 (6 months) for both groups (see Table 2), will be: (1) self-efficacy measured with the *Self-Efficacy for Managing Chronic Disease* scale [61]; (2) self-management practices, with the *Self-monitoring and Insight* sub-scale of the *health education impact questionnaire* (heiQ [62,63]; (3) health habits, using the questionnaire developed as part of the PRECISE study [64]; (4) patient activation, with the *Patient Activation Measure*[65]; and (5) psychological distress, with the *Psychological Distress Scale*[66].

**Table 2 T2:** Proposed study plan

	**Visit 1**	**Visit 2**^**1**^	**Visit 3**	**Visit 4**	**T3**^**2**^
	**T0**		**T1**	**T2**	
Time from the start of the intervention	−2 weeks	0	3 months	6 months	12 months
Verification of eligibility	√				
Informed consent	√				
Covariables: Socioeconomic level, social isolation, literacy, mental health and multimorbidity	√				
Proximal outcomes: Personal self-efficacy, self-management practices, lifestyles, activation and psychological distress	√		√	√	
Intermediate outcomes: Empowerment, quality of life and use of services	√			√	√

^1^ Visit 2 will mark the beginning of the intervention. This will be two weeks after randomization for the experimental group and 6 months after randomization for the control group.

^2^ For the experimental group and use of services only.

Intermediate outcomes, evaluated at T0 and T2 (see Table 2), will include: (1) empowerment, measured with the heiQ scale [62]; (2) quality of life, measured with the SF-12v2 scale [67]; and (3) the use of health services, measured using clinical data from the CSSS (with Magic Chronique software by MediaMed) for hospitalizations, emergency room visits and CSSS services (e.g., psychosocial services or specialized services related to the specific CD), and electronic data on visits with physicians and nurses in the FMG.

A number of covariables will also be documented (T0) to describe participant characteristics: (1) socioeconomic status with family income and patient perceptions of his or her economic situation; (2) social isolation, measured with the social isolation subscale of the *Nottingham Health Profile*[68]; (3) literacy, measured with the *Newest Vital Sign*[69]; (4) mental health, measured with the *Hospital Anxiety and Depression Scale* (HADS) [70,71]; and (5) multimorbidity, measured with the *Disease Burden Morbidity Assessment* (DBMA) [72]. French versions are available for all validated instruments. When selecting data collection instruments, valid shorter versions were preferred to reduce completion time. Considering the circumstances of the vulnerable clientele, questionnaires will be self-administered in the presence of a research assistant who will provide the required assistance to the participant, ranging from minimal supervision to reading all the questions, if and when needed. If the patient cannot travel, the questionnaires can be administered by telephone or at the participant’s home.

The evaluation component will be conducted according to the study plan described in Table 2.

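### Table 2 contradicts the text on when controls are measured: as tabulated, control T1 and T2 fall during or at the end of the controls' own delayed intervention, not under usual care

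*Protocol article*

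**What the plan says.** The schedule is in the Measures section, Table 2. Its time row is headed "Time from the start of the intervention" and gives T0 at minus 2 weeks, Visit 2 at 0, T1 at 3 months, T2 at 6 months and T3 at 12 months. Footnote 1 defines the zero point, "Visit 2 will mark the beginning of the intervention", and continues: "This will be two weeks after randomization for the experimental group and 6 months after randomization for the control group". Footnote 2 limits only T3 to one group: "For the experimental group and use of services only". T0, T1 and T2 therefore apply to both. The Measures section closes by making Table 2 the plan by which the evaluation is run.

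The surrounding text describes something else:

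- Measures, on the proximal outcomes: "evaluated at T0 (recruitment period), T1 (3 months) and T2 (6 months) for both groups". It gives no origin for the 3 and 6 months.
- Study population, on controls: they "will receive the usual care for six months and then the same intervention as the treatment group for the following six months".
- Study population, on the order of events: "After verifying patient eligibility and obtaining their consent, participants will be allocated to one of two groups". The envelopes are opened at recruitment.
- The Data analysis plan for the effects evaluation compares the groups at T1 by analysis of covariance adjusted for T0, and compares change over time for the six-month outcomes.
- Economic analysis: the comparator is usual care.

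**The concern.** The randomized comparison needs control measurements taken before controls receive the intervention. Table 2 is the only place that gives T1 and T2 an origin, and that origin is the start of the intervention, which comes some five and a half months later for controls than for the experimental group. Staff who book visits from the table would question controls partway through and at the end of their own programme. Questionnaires not collected during the usual-care period cannot be recovered afterwards. The planned analyses at T1 and T2 would then compare two groups with the same exposure.

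**Working it through.** **Inputs.** Visit 2 is 2 weeks after randomization (experimental) or 6 months after it (control), from footnote 1. The offsets come from the time row of Table 2. Two weeks is 14/30.4375 = 0.46 month.

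**Step 1: Table 2 read literally.** Time since randomization = time of Visit 2 + offset.

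| | Experimental (months) | Control (months) |
|---|---|---|
| T0 | 0.46 − 0.46 = 0 | 6 − 0.46 = 5.54 |
| Visit 2 | 0.46 | 6 |
| T1 | 0.46 + 3 = 3.46 | 6 + 3 = 9 |
| T2 | 0.46 + 6 = 6.46 | 6 + 6 = 12 |

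Study population gives controls usual care in months 0 to 6 and the intervention in months 6 to 12. The tabulated control T1 falls midway through the intervention and T2 at its end. Neither falls under usual care.

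**Step 2: the T0 column.** It carries eligibility and consent, which Study population places before allocation. T0 is therefore at or before month 0 in both groups. For controls the gap from T0 to Visit 2 is then at least 6 months, whereas the table says 2 weeks. The column works for the experimental group (0.46 − 0.46 = 0) and cannot work for controls.

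**Step 3: what following the table would do to the comparison.** The plan's own power figure comes first, from Sample size and statistical power: effect 0.5 SD, 200 per group, 25 per nurse, intracluster correlation 0.10, two-sided 5%, power 80%.

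- Design effect = 1 + (25 − 1) × 0.10 = 3.4.
- Unclustered n = 2 × (1.960 + 0.842)² / 0.5² = 62.8 per group; × 3.4 gives 214, against 200 stated.
- At 200 per group the standard error is √(2 × 3.4/200) = 0.184 SD. Power = Φ(0.5/0.184 − 1.960) = 77%, close to the stated 80%.
- If only the experimental group is clustered by nurse, the standard error is √(3.4/200 + 1/200) = 0.148 SD and power is 92%.

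The small gap between 77% and 80% is not part of this point. On the tabulated schedule both groups have had 3 months of intervention at T1 and 6 months at T2. If the effect at equal exposure is the same in both, the expected difference is 0 and the chance of rejecting is the 5% error rate, against 77% to 92% for a true 0.5 SD contrast with usual care.

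**Step 4: the text's reading.** With T1 and T2 at 3 and 6 months after recruitment for both groups, control T1 lies wholly within usual care and T2 at its end, so the contrast exists. One mismatch remains. Six months of intervention from a start at 0.46 month puts the experimental T2 at 6.46 months, while controls start at 6. A control T2 at the same time since randomization falls 6.46 − 6 = 0.46 month, about two weeks, into the controls' intervention. A control T2 at 6 months avoids this but leaves follow-up two weeks shorter than in the experimental group. The article does not say which applies.

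**The case against.** The strongest reply is that the literal schedule cannot be carried out and so cannot be the plan. Nobody obtains consent five months after randomizing, so the time row was probably written with the experimental group in mind. Footnote 1 hangs on Visit 2 and does not itself move T1 or T2. A usual-care comparison is intended throughout: Study population, Measures, Data analysis plan and Economic analysis all describe it, and Strengths and limitations restricts talk between nurses during the first six months, which makes sense only if the comparison is made then.

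Much of this stands. A reader might infer from Table 2 that every control measurement is shifted and that the trial has no usual-care contrast. The article does not support either inference. At T0 the table contradicts itself rather than shifting consistently, and the text plainly intends the contrast. The zero difference is likewise not a forecast. It needs the table to be followed and the effect to be equal in both groups.

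What does not stand is that the matter is only clerical. Footnote 1 names the control group, footnote 2 exempts only T3, and the article makes Table 2 operative. Nothing in the text times control T1 and T2 explicitly from randomization or says that control T2 precedes Visit 2. The two-week mismatch also survives the charitable reading, although it would dilute the T2 contrast only slightly and leaves T1 untouched.

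**Conclusion.** Wrong as written: the operative visit table and the text give incompatible measurement times for controls. As tabulated, control T1 and T2 lie about 5.5 months later after randomization than the experimental visits (9 − 3.46 = 5.54; 12 − 6.46 = 5.54), with no usual-care follow-up shown. The text intends a comparison with usual care, so the loss of that comparison is conditional on the table being followed, and a difference near zero further assumes equal effects in both groups. The two-week overlap at T2 depends on a time-matched control visit, which the article neither requires nor rules out. The timing results rest only on adding the footnote's start times to the table's offsets.

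**What to change.** 1. Replace the time row of Table 2 by time from randomization, on the same clock in both groups, with T0 before allocation.
2. State that each control patient's T2 is completed before that patient's Visit 2.
3. Reconcile footnote 1 and the two-week offset with Study population and the Measures text, and say which time since randomization T2 has in each group. If T2 were at 6 months from randomization and the tabulated starts stood, experimental patients would have had 6 − 0.46 = 5.54 months of intervention by then. The sponsor should state the exposure intended.
4. Give any control measurements taken around the delayed intervention their own labels, and keep them out of the randomized comparison.

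The cost is rewording the table and the visit schedule. It needs no extra patients and no extra visits for the randomized comparison.
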